#### Comparison

Standard care is the usual care at the participating site. This will vary by site and according to individual patient symptoms but the minimum is generally an annual visit plus ECG/EKG. Other care may include appropriate history taking, physical examination, ECG/EKG (or more in depth cardiac investigations), pulmonary and gastrointestinal investigations, and rehabilitation measures.

All control group participants will visit their trial site at baseline and months 5, 10 and 16 months post intervention (that is, 16 months from baseline) for the measurements as detailed in Appendix.

### Study and safety assessments

A number of factors affecting the trial population suggest that we would expect to observe a larger than normal incidence of episodes of adverse events (AEs) such as fatigue and ill health due to co-morbidities of the study population. All known disease progression and co-morbidities will be noted but not reported.

Due to the large amount of co-morbid diseases that we expect to be present in the population, we will record, but not report, Serious Adverse Events (SAE) in the following categories:Any new cardiovascular event,Any new treatment of myotonic dystrophy type 1,Any hospitalisation due to falls or fractures,Any hospitalisation due to exacerbation of an existing medical condition, andAny elective or planned investigation or treatment.

All unexpected SAEs (that is, an SAE that is not listed above) will be recorded and reported to the sponsor. An example of an unexpected SAE would be premature death of a participant that was not due to an existing condition.

Safety assessments will be recorded at every visit.

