## Background

Myotonic dystrophy type 1 (DM1) is a rare, inherited, progressive disease as well as an autosomal dominant multi-systemic disorder. It is one of the most common adult forms of muscular dystrophy, with a prevalence of approximately 10 per 100,000 people affected [1, 2]. With 733 million people in Europe, we estimate that 75,000 are DM1 patients [3]. Typical symptoms of the disease include progressive muscle weakness and wasting from distal to proximal, ptosis; weakness of facial, jaw and anterior neck muscles; myotonia; daytime sleepiness; fatigue and cataracts. Other symptoms of adult DM1 include cardiac conduction defects, as well as endocrine, gastrointestinal and cognitive dysfunction. DM1 is one of the most variable human diseases, has complex, multi-systemic and progressively worsening clinical manifestations and leads to severe physical impairment, restricted social participation and premature death [4, 5].

There is no pharmaceutical treatment for causal or symptomatic relief of DM1 core symptoms, with the exception of Modafinil for excessive daytime sleepiness and mexiletine for myotonia. Thus, the aim of treatment is to relieve impairments, reduce limitations and optimise participation. Physical activity has been acknowledged as an important factor for health in general. For patients with a slowly progressive neuromuscular disease, such as DM1, there is accumulating evidence for prescribing low-to-moderate-intensity strength and aerobic exercise training, and an active lifestyle [6]. Nevertheless, recent reviews conclude that existing studies are limited in number and quality, and that there is a need for disease-specific, randomised, controlled trials investigating the effect on quality of life [6–8].

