## Methods/Design

### Study description

OPTIMISTIC is a two-arm, multi-centre, randomised controlled trial designed to compare cognitive behavioural therapy, plus graded exercise against standard patient management regimes. It is expected that the trial and outcome work will lead to new clinical guidelines for DM1 management. The intervention comprises cognitive behavioural therapy (CBT) and graded exercise therapy, both of which aim to achieve a more active lifestyle.

The effectiveness of this intervention, together with any adverse events associated with it, will be compared to standard patient management. Outcome measures will be measured at baseline; 0 to 5 week period depending if separate screening and baseline visits are required, 5 months (± 1 month, 10 months (± 1 month, the end of the intervention period) and at 6 months (± 1 month) post intervention (that is, 16 months from baseline, Fig. 2).

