### Trial management and oversight arrangements

OPTIMISTIC will have the following two oversight committees:The Trial Management Committee will be responsible for day-to-day operational issues.The External Advisory Board will be responsible for strategic decision making and issues linked to monitoring ethical and patient safety issues, together with monitoring recruitment and data quality issues.

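### The serious adverse event reporting exemption covers new cardiovascular events and hospitalised falls or fractures, with no exception for fatal or possibly exercise-related events and no stated by-arm review

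*Protocol article*

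**What the plan says.** The section Study and safety assessments sets the rule. It gives its reason as "Due to the large amount of co-morbid diseases that we expect to be present in the population" and then says "we will record, but not report, Serious Adverse Events (SAE) in the following categories". The five categories include "Any new cardiovascular event" and "Any hospitalisation due to falls or fractures". Hospitalisation for worsening of an existing condition is a separate category on the same list. The next paragraph defines what is reported: "All unexpected SAEs (that is, an SAE that is not listed above) will be recorded and reported to the sponsor". Its example is an early death that no existing condition explains.

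Other sections bear on this:

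- Background describes the population: "Other symptoms of adult DM1 include cardiac conduction defects", along with progressive muscle weakness.
- Behavioural change intervention offers a graded walking programme or a fitness programme of moderate-intensity exercise, at least half an hour three times a week.
- Study description promises a comparison: "The effectiveness of this intervention, together with any adverse events associated with it, will be compared to standard patient management".
- Trial management and oversight arrangements gives the External Advisory Board responsibility for "issues linked to monitoring ethical and patient safety issues". The Board's own section says it is consulted at least once a year, or more often if it asks.
- Consenting participants says that new safety information which changes the risk-benefit assessment will lead to revised documents and renewed consent.

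**The concern.** Exempting anticipated events from individual reporting is a normal device. It fits events that the disease would produce anyway and that say little about the intervention. These two categories do not fit that description. Cardiac events and injurious falls are the serious harms one would watch for when people with conduction defects and weak muscles are asked to exercise more.

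What is at stake is recognition during the trial. The sponsor is not sent these events one by one. If nobody pools them by arm either, an excess in the intervention group could pass unnoticed while participants are still exercising. The commitment to act on new safety information depends on somebody seeing that information.

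**Working it through.** The point rests on wording, so there is no figure in the plan to reproduce. The checks set the sections side by side.

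**1. Does the reason cover the exemption?** The stated reason is co-morbidity. Worsening of an existing condition already has its own line on the list. The cardiovascular line applies to new events, so it goes beyond the reason given. The falls and fractures line makes no distinction between background falls and falls during prescribed activity. Neither line excludes events judged possibly related to the intervention.

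**2. Are deaths covered?** An unexpected event is defined as one that is not on the list. A fatal new cardiovascular event is on the list, so by the definition it is not reported. The example in the same paragraph makes a premature death reportable if no existing condition caused it, and a death from a genuinely new cardiovascular event fits that. The example may not settle the matter either: conduction defects are a feature of DM1, so one site could attribute a cardiac death to the existing disease and another could call it new. The text does not say which rule prevails.

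**3. Who sees the exempt events by arm?**

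| Body | Stated role | Stated access to exempt events by arm |
|---|---|---|
| Sponsor | Receives events not on the list | None |
| External Advisory Board | Patient safety; may terminate the trial | None stated |
| Trial Management Committee | Day-to-day operations; meets at least monthly | None stated |
| Treating clinician, therapist, nurse | Review of individual patients | Not applicable |

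**4. Timing.** Recruitment began on 6 April 2014 and the study is due to end on 31 October 2016. That is 939 days, and 939 / 30.44 = 30.8 months. A guarantee of one consultation a year gives two or three consultations in that time. The permitted gap of 12 months exceeds the 10-month intervention by 2 months.

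**5. Would an imbalance show without pooling?** The documents give no event risk, so the risks below are assumptions shown over a range. With n = 148 per arm, expected events are n × p. Power at the two-sided 5% level, treating participants as independent, is

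Φ{ [|p2 − p1| − 1.96 √(2 p̄(1 − p̄)/n)] / √([p1(1 − p1) + p2(1 − p2)]/n) }.

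| Assumed risk, control vs intervention | Expected events | Power |
|---|---|---|
| 2% vs 4% | 3.0 vs 5.9 | 17% |
| 5% vs 10% | 7.4 vs 14.8 | 37% |
| 10% vs 20% | 14.8 vs 29.6 | 68% |

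For the middle row: p̄ = 0.075, the null standard error is 0.0306 and the alternative standard error is 0.0305. Then (0.05 − 1.96 × 0.0306) / 0.0305 = −0.33, and Φ(−0.33) = 0.37.

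The largest expected site share in Sample size calculation is 33%. In the middle row that site would see 7.4 × 0.33 = 2.4 control events and 14.8 × 0.33 = 4.9 intervention events over the whole trial. No site could recognise a doubling from such counts. Only a pooled table by arm could suggest it, and even that would call for judgement, not a test.

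**The case against.** The strongest reply is that much of the alarm comes from silence. The rule contrasts recording with reporting to the sponsor, so it governs individual reports to the sponsor and nothing more. It does not deny the Board the recorded events. The Board has a safety remit, can ask to be consulted more often, and can end the trial for clinical reasons. A journal article commonly leaves the content of Board tables to the full protocol or the Board's terms of reference. Recording is complete, so the comparison between arms remains possible at the end. This stands, and it rules out several stronger readings.

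- A reader might infer that these events are hidden from everyone until database lock. The text does not say so; it only fails to show a route.
- A reader might infer that no review could happen while participants exercise. A clinician judges safe activity beforehand, therapists stay in contact with that clinician, therapists or nurses may ask for a review at any time, and withdrawals from the intervention because of adverse events are logged. What these routes lack is a view across participants and arms.
- A reader might infer that fatal cardiovascular events are plainly exempt. They are ambiguous, as shown above.
- A reader might infer that more contact in the intervention arm biases the adverse event comparison. The Appendix schedules adverse events at the same visits in both arms, and the weekly calls are for homework and attendance. Bias is possible but not shown, and it is no part of this point.

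The reply does not reach the rule itself. The exemption is explicit, its reason does not fit new events, and it has no exception for death or relatedness.

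**Conclusion.** The point holds as a defect in how the exemption is drawn and in how it connects to safety oversight. Three things rest on the text: two categories on a plausible harm pathway are exempt from reporting to the sponsor, for a reason that does not cover them; the rule for deaths is ambiguous; and no by-arm route to the Board is shown. That an imbalance could go unrecognised during the trial is an inference from the third, and it depends on no such route existing in documents not shown here.

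The number of events affected is unknown. The counts and power figures rest on assumed risks and only illustrate why pooling matters; the conclusion does not depend on them. No figure in the plan is wrong and the final comparison is not invalidated. This is an inexpensive improvement to participant protection, worth making while the trial is still recruiting.

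**What to change.** 1. Take new cardiovascular events and hospitalised falls or fractures off the exempt list. At the least, exclude from the exemption any event that is fatal or possibly related to the intervention.
2. State that all deaths are reported to the sponsor, which removes the conflict between the list and the example.
3. State that the External Advisory Board receives, at each consultation, a by-arm table of all recorded serious adverse events, including the categories that stay exempt.
4. Reconcile Study and safety assessments with the commitment on new safety information in Consenting participants and with the Board's role in the two oversight sections. If the full protocol or the Board's terms already provide the table, a cross-reference is enough for item 3.

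The cost is revised wording, some additional serious adverse event forms and one table per Board consultation. The events are already being recorded, so no new data collection is needed. The sample size and the efficacy analysis do not change.

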### Data collection and management

#### Data collection

It is the responsibility of the local PI to ensure the accuracy of all data entered and recorded in the CRFs and the database for his or her site. The Delegation of Responsibilities Log will identify all trial personnel responsible for data collection, data entry and handling and managing the database.

The data will be collected by the PI or delegate onto a paper CRF for subsequent transcription to the eCRF. Data entry onto the web based eCRF may be done locally or paper CRFs may be sent to an external unit for data entry depending on local preference. If CRFs are sent away for data entry a copy of what is sent must be retained by the originating team. This includes patient-completed questionnaires. The two copies must always record the same information. This means that if values are updated as a result of the querying process the changes must be annotated on both copies, initialled and dated. Both physical and electronic storage of data will protect the security of these data and the confidentiality of participants.

The study questionnaires will be completed according to the schedule shown in Appendix by the participant with the assistance of the research nurse and caregivers. Laboratory derived blood tests will be held on local clinical databases in an identifiable format and for a time frame in line with local regulations and policies for clinical care systems. All research blood samples will be processed and stored at each site (as per Sample Analysis and Chain of Custody Plans in the Study Operations Manual) and transported to the relevant laboratory for analysis at timeframes outlined in the Study Operations Manual for batch analysis.

The medical notes can act as source data for past medical history, subsequent medical conditions, hospital admissions, diagnostic reports and blood and urine results.

#### Data management system

A data management system will be provided by TCTU using OpenClinica (https://www.openclinica.com/), its standard Good Clinical Practice (GCP)-compliant data management system. The study system will be based on the protocol and CRF for the study and individual requirements of the investigators. Development and validation of the study database, quality control and extraction of data will be done according to TCTU procedures.

### Statistics and data analysis

#### Sample size calculation

The primary outcome is the DM1-Activ scale, which is a Rasch-built measure of activity and participation for patients with DM1 and is currently the best such measure for these patients. Based on a minimum clinically important mean difference of 1.4 on the 40-item DM1-Activ scale, standard deviation of 3.5 and effect size = 0.4, 80 % power and 5 % significance level, we need a sample size of 100 in each arm, or 200 in total.

DM1 is a genetic condition so it is likely that some members of the same family will take part in the study. To avoid the risk of contamination, immediate family members (mother, father, children, and siblings) will be allocated to the same group, with the first family member being randomly allocated and subsequent members being assigned to the same group as the first. This means that there will be some clusters of more than one individual and the sample size needs to be inflated to account for this. Newcastle estimates that this may affect 50 % of their participants, the other sites estimate that fewer than 10 % of participants will be part of a family group. All sites estimate that almost all family groups will comprise two individuals. Using estimates of distributions of recruitment across sites (Newcastle = 23 %; Nijmegen = 30 %; Paris = 33 %; and Munich = 13 %) and the above family group proportions gives an average cluster size of 1.17. Using a conservative intra-cluster correlation coefficient of 0.20, gives an inflation factor of 1.035, meaning the recruitment target needs to be increased by 10 to 296. After allowing for up to 30 % drop-out this gives a final sample size of 208, or 104 participants per arm.

These are conservative estimates (especially the minimum clinically important difference). The clinical OPTIMISTIC sites between them see well over 1,000 DM1 patients per year, which gives OPTIMISTIC a good pool of potentially eligible participants. Around 70 % of DM1 patients are expected to be eligible for OPTIMISTIC.

We will be using one of our secondary outcomes, the 6-minute walk test (6MWT) as an additional validation of the DM1-Activ scale, meaning that we have also powered this secondary outcome. The DM1-Activ sample size of 208 gives over 90 % power for the 6MWT based on a mean difference of 40 m, standard deviation of 80 m and a baseline of 450 m.

#### Proposed analysis

The primary analyses will be conducted according to the principles of intention to treat (ITT) as outlined on the ICH E9 ‘Statistical Principles for Clinical Trials’.

Continuous variables will be summarised by the number of observations, number of missing values, mean, standard deviation (SD), median, inter-quartile range (IQR) and range. Summaries will be provided at baseline, at each subsequent time point and for the change from baseline by intervention group. Categorical variables will be summarised by the number of observations, number of missing values and number and percentage in each category. Summaries will be provided at baseline and at each subsequent time point.

The primary outcome and most other outcomes are continuous and so linear models will be utilised. The primary outcome of change in DM1-Activ will be analysed using mixed effects (repeated measures) regression models. Models will include fixed effects for intervention group, time point, and their interaction, plus random effects for each subject to account for repeated measures, and will assume a general covariance structure. A binary variable will be added to the regression model to represent the difference between the intervention and standard care. The minimisation variables of severity of DM1 (measured using the MIRS 5-point scale) and caregiver involvement at baseline will also be added to the regression model as fixed effects, as well as stratification by site.

Intervention effect differences will be reported with 95 % confidence intervals (CIs) and *P*-values. Results will also be explored and reported with additional *a priori* adjustment for potential effect modifiers (see list in *Measures used as potential effect modifiers*). Subgroup analyses will be carried out by first testing for a subgroup factor by intervention interaction [16]. If this is significant at the 5 % level, results will be estimated separately by the different subgroups. These analyses will also be repeated for all the secondary outcomes. Appropriate transformations of outcomes will be performed where necessary to satisfy modelling assumptions.

A statistical analysis plan (SAP) will be written prior to datalock and approved by the statistician and CI. Analyses will be carried out using SAS.

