#### Participant selection and enrolment

##### Identifying participants

The study will be conducted on an outpatient basis. The primary route of participant recruitment will be through their neurologist at myotonic dystrophy clinics and neuromuscular centres in the UK, the Netherlands, Germany and France. At each centre, the PI and neurological physicians will be assisted by the study research nurses who will identify potential participants by assessing inclusion and exclusion criteria.

Additionally, participants will also be recruited from the local or national registries of individuals with DM1. Currently, the registries for France, Germany, the Netherlands and the UK contain 1,500, 500, 400 and 300 registered individuals, respectively. Registries contain patients who have specifically shown interest in participating in research and previously consented to be contacted about research in which they can take part. Registries will contact all potentially eligible participants providing a Patient Information Sheet (PIS) and local contact details as well as contacting medical professionals who have shown an interest in the condition to increase awareness beyond the trial sites.

As DM1 is a genetic condition, it is likely that some members of the same family will wish to participate in the study. Immediate family members (mother, father, children, and siblings) may request to attend together for screening and subsequent study visits or separately at a later date. There is no time limit on when a subsequent family member can attend for screening. To avoid treatment contamination, immediate family members will be allocated to the same group, with the first family member being randomly allocated and subsequent member(s) being assigned to the same group as the first. The web-based Tayside Randomisation SysTem (TRuST) will assign the initial family member as per stratification and minimisation criteria (see *Randomisation*), with subsequent family member(s) being assigned by TRuST into the same group. All participants will be asked for consent to allow the study team to enquire if another member of their immediate family is enrolled into OPTIMISTIC. Their name will be required to review the randomisation log to establish their study ID. The study ID of the initial family member will be entered into TRuST, thereby allowing same group allocation.

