
The intervention will be delivered by therapists who have received extensive training before the trial starts and will use a standardised treatment manual developed by the OPTIMISTIC team. Prior to participating in the graded activity module, the treating clinician will make a judgment as to the degree of physical activity the participant is safely capable of doing, which will be communicated to the therapists. The therapists will remain in contact with the treating clinician throughout the trial to discuss any changes. The therapists and/or the research nurse can request that the treating physician/Investigator to review the patient at any time if any of the research team, the patient or the carer have any concerns. If required, the patients’ GP will be informed.

Participants will receive a workbook containing relevant information and assignments. If deemed appropriate a patient may be given a gym membership to assist with their set goals. If participants give their permission, CBT sessions will be audio recorded and transcribed. Transcriptions will be anonymised. Audio recordings will be stored securely at local sites and destroyed as described under *Study record retention*.

Between sessions participants will do ‘home-work’ assignments that are discussed in the subsequent session. If caregivers are involved in the intervention, they will be asked to support the patient in carrying out these assignments. Treatment integrity will be determined by two experienced cognitive behavioural therapists, who will independently rate a random selection of audio-taped sessions. During the intervention period phone calls to participants will be made at least once a week between sessions to remind them to complete any homework and to ensure attendance at sessions. Where it is felt necessary and resources allow participants will be visited in their homes to increase adherence and provide support where needed.

The intervention runs for 10 months but is front-loaded, meaning the first 4 months can be considered the ‘active’ phase with the remaining 6 months in the ‘booster’ phase. In this period of 10 months a patient will receive 10 to 14 sessions; at least 5 of them are face to face sessions. For the other sessions the therapist can decide, dependent on the traveling distance and the mobility of the patient, to use telephone contact or video conferencing as an alternative.

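### The sample size is inflated for relatives allocated together, but the stated primary model has no family term, so its standard errors are slightly too small

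*Protocol article*

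**What the plan says.** **Allocation.** Under Identifying participants, to avoid contamination, "immediate family members will be allocated to the same group": the first relative is randomised and later ones follow. The Randomisation section repeats the rule and says that the first relative's study ID is entered into the randomisation system.

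**Sample size.** The Sample size calculation starts from a "minimum clinically important mean difference of 1.4 on the 40-item DM1-Activ scale", with "standard deviation of 3.5 and effect size = 0.4" and "80 % power and 5 % significance level", and concludes "we need a sample size of 100 in each arm, or 200 in total". It then turns to families and says that "there will be some clusters of more than one individual and the sample size needs to be inflated to account for this". It uses an average cluster size of 1.17, an intra-cluster correlation (ICC) of 0.20 and a factor of 1.035. This adds 10 to the recruitment target, giving 296, with 208 expected to complete.

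**Analysis.** The Proposed analysis describes the primary model as follows: "Models will include fixed effects for intervention group, time point, and their interaction, plus random effects for each subject to account for repeated measures". It mentions a general covariance structure and adds MIRS severity, caregiver involvement and site. It asks for 95% confidence intervals and P-values, and repeats the analyses for the secondary outcomes. No family effect, cluster-robust standard error or other family adjustment appears there or elsewhere in the article.

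**The concern.** For participants with an enrolled relative, the unit of allocation is the family. The sample size section accepts this and recruits extra patients for it, but the model section does not use it. The subject random effects have a stated purpose, the repeated measures within a person, so they cannot also absorb correlation between two people. Site as a fixed effect removes differences between sites, not similarity between relatives within a site.

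When whole clusters fall in one arm and the correlation is positive, an analysis that assumes independence gives a standard error for the arm difference that is too small. Confidence intervals are then too narrow and P-values too low. The allocation factors (site, MIRS, caregiver) are carried into the model, but the family rule, which is also part of the allocation, is not.

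**Working it through.** **Inputs, all from the Sample size calculation:** difference 1.4, SD 3.5, power 80%, significance 5% (two-sidedness is assumed, because it reproduces the stated size), drop-out 30%, ICC 0.20, cluster size 1.17, factor 1.035. Recruitment shares are 23% at Newcastle and 30%, 33% and 13% at the other three sites. Half of Newcastle participants and fewer than 10% elsewhere are expected to be in family groups, almost all of them pairs.

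**1. Reproduce the plan's figures.**
- Per arm: 2 × (1.960 + 0.842)² / 0.4² = 98.1, so 99 by the normal formula. The t-based solution is 99.08, which rounds up to the stated 100.
- Drop-out: 200 / 0.7 = 285.7, so 286. Then 286 × 1.035 = 296.0, as stated.
- Completers: 296 × 0.7 = 207.2 and 200 × 1.035 = 207, in line with 208.
- Share of participants in pairs, f = (0.23 × 0.50 + 0.76 × q) / 0.99, where q is the share at the other sites. At q = 7%, f = 0.170 and the participant-weighted cluster size is 1 + f = 1.17, as stated. At q = 10%, f = 0.193 and the size is 1.19.
- Design effect: 1 + (1.17 − 1) × 0.20 = 1.034, against the stated 1.035.

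The plan's figures hold together, so 1.035 can be used as its own measure of the clustering.

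**2. Effect of leaving family out of the model.**
- Model-based SE / true SE = 1 / √1.035 = 0.983, so the SE is about 1.7% too small.
- True two-sided level = 2 × [1 − Φ(1.960 / √1.035)] = 2 × [1 − Φ(1.927)] = 0.054.
- Coverage of a 95% interval = 1 − 0.054 = 94.6%.
- With q at its 10% limit the design effect is 1.039 and the level 0.0545.

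**3. Simulation check.** 208 participants, pairs always in one arm, ICC 0.20, one outcome per person, ordinary t-test, 40,000 replicates. Rejection under the null was 0.056 with 17% of participants in pairs, 0.055 with 19%, and 0.049 with no families. Monte Carlo error is √(0.05 × 0.95 / 40,000) = 0.001. Direction and size agree with the formula.

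**4. Power.** Power = Φ(0.4 × √(n/2) − 1.960).
- Families ignored, n = 104 per arm: 82.2%.
- Families allowed for, n = 104 / 1.035 = 100.5 per arm: 80.9%.

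The planned sample therefore already covers the correct analysis.

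**The case against.** **The error is small and may be smaller still.** The plan calls its ICC of 0.20 conservative. Site and MIRS as fixed effects may explain part of the similarity within families. Drop-out breaks up pairs: if relatives drop out independently (an assumption), the design effect falls to about 1 + 0.17 × 0.7 × 0.20 = 1.024 and the level to about 5.3%. All of this stands and bears on severity, but it does not change the direction of the error.

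**The SAP could add the term.** The section is headed as proposed analysis, its list of effects is not said to be complete, and a SAP is to follow before data lock. This limits the harm. It does not remove the mismatch, because the protocol names the random effects and omits the one that its own sample size implies. A SAP that copied the sentence would copy the gap.

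**Stronger readings that a reader might infer, and why they fail.**
- *A much larger inflation of the test.* An ICC of 0.5 would give a design effect of 1 + 0.17 × 0.5 = 1.085 and a level of about 6.0%, but the only ICC in the article is 0.20. Newcastle's high family rate is already averaged into 1.035 and is not a separate error in the primary test.
- *Therapist clustering as part of the same fault.* The article says that "The intervention will be delivered by therapists who have received extensive training before the trial starts", so only one arm is nested in therapists. It gives neither a therapist count nor a therapist ICC, and it makes no allowance for therapists that the model then fails to honour. That is a silence, not a contradiction, and any size attached to it would be invented.
- *The covariance wording blocks a family effect.* The general covariance structure is not defined closely enough to say that the subject effect is redundant. Even if it were, family is a higher level and its term can be added under either reading.

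**Conclusion.** The point holds and is minor. The protocol recruits for family clustering and then states a primary model that treats relatives as independent. On its own design effect of 1.035, standard errors are about 1.7% too small, the 5% test runs at about 5.4%, and 95% intervals cover about 94.6%. Only a result close to the significance boundary could change.

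The size rests on the plan's ICC of 0.20 applying to the 10-month treatment contrast, on its forecast of family participation, and on the model being fitted as stated. The anti-conservative direction needs only a positive correlation between relatives. The same applies to each secondary outcome analysed with this model, to the extent of its own family correlation.

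**What to change.** In the Proposed analysis, and in the SAP before data lock, add a random intercept for family to the primary model. Nest subject within family and count participants without an enrolled relative as families of one. Define family by the linkage used at randomisation. Apply the same model to the secondary outcomes.

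State the fallback in advance: if the family variance is not estimable, report family-clustered empirical standard errors. This is a realistic case, because 208 × 0.17 / 2 gives only about 18 complete pairs to estimate it from, and fewer if drop-out splits pairs.

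The cost is one sentence of analysis text and one model term. Confidence intervals widen by about 1.7% (√1.035 = 1.017) on the plan's inputs. The sample size does not change, no new data are needed, and power stays at about 81% with 208 completers.
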